**Research Protocol**

Synopsis

This pragmatic trial with cluster randomization of AEDs is designed to evaluate the effectiveness and cost-effectiveness of screening methods (modified PAT vs FAST vs modified SASQ) and interventions (Leaflet vs Brief advice vs Brief counselling) in routine AED care. Due to the design implications of a multi-level factorial design in AEDs the proposed trial involves a universal screening approach in which relevant data for a sub-sample of linked presentation population is collected. Therefore, the trial design encompasses a 3x3 factorial trial, screening method (modified PAT vs FAST vs modified SASQ) and intervention (Leaflet vs Brief advice vs Brief lifestyle counselling). The main advantages of utilising a factorial approach are twofold. First each of the three elements (screening tool and intervention) can be analysed independently with sufficient power to make meaningful interpretation of relative effectiveness. Second, the method enables meaningful interpretations of the relative effectiveness of any combination of screening method and intervention. Because the universal screening population encompasses a sub-group of linked presentation targeted population we can make meaningful comparisons of the relative effectiveness and interactions associated with screening approach in AEDs. Nine AEDs across the North East, London and the South East Regions of England will be recruited. AEDs will be randomly allocated to one of three intervention conditions: the patient information leaflet control condition (n=3), the structured brief advice condition (n=3); and lifestyle counselling by an Alcohol Health Worker (n=3). To test the relative effectiveness of different screening methods all AEDs will be randomised to either a modified single item screen (Single Alcohol Screening Question; M-SASQ) or a modified Paddington Alcohol Test (SIPS-PAT) or FAST Alcohol Screening Test (FAST) screening method. AEDs in the modified PAT condition will use targeted screening as per the standard PAT protocol. AEDs in the FAST and modified SASQ conditions will use universal screening for case identification and collect information about whether a patient would be part of a linked presentation group and then use statistical simulation to analyse any interactions. Screening randomisation will be stratified by median AED admission rates (2 levels) and intervention condition (3 levels). Each AED will recruit a minimum of 131 patients who are hazardous or harmful drinkers into the trial and a short baseline assessment will be carried out. Outcome will be assessed at 6, and 12 months after intervention. Outcomes will include system implementation outcomes and patient outcomes. We will also examine the practitioner and organisational factors associated with successful implementation.

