The sample size calculation is designed to account primarily for intervention level outcomes. Powering the study in this way will also account statistically for appropriate outcomes for screening approach and screening method. The primary outcome for this study is the proportion of patients who consume alcohol within recommended levels at 6 month follow up. Recent meta-analysis (Moyer et al 2002) suggest that the difference between brief intervention and control is of the order 13%, 5% reduction in the control group and 18% in the brief intervention group. In order to detect a difference of this magnitude at the 5% significance level with 80% power, for a 2-sided test, requires 109 patients in each of the 3 groups, a total of 327. Our experience with other multi-centre randomized controlled trials of interventions for alcohol use disorders suggests that with assiduous follow-up the potential loss to follow-up across groups is of the order 25%. Taking this loss into accounts inflates the sample required to 131 in each group, a total of 393 patients per intervention.

The proposed study involves a cluster design and requires a statistical adjustment to account for any potential cluster effect. The literature, and our previous experience of trials in primary care, suggest an intra-class correlation coefficient of 0.04 is appropriate. Assuming a cluster size of the order 131 patients this inflates the sample size calculation by a factor of 2.7 requiring patients 393 in each group, a total of 1179, with an expectation that at least 882 will be followed up at 6 months.

We propose to recruit 9 AED’s. AED populations will be screened using 1 of 3 screening method groups (3 AED’s in each group) and will receive 1 of 3 intervention (3 AED’s in each group).

Planned analysis

As the study is pragmatic in design, the planned analysis will be by intention to treat. The primary outcome is dichotomous in nature, drinking within or above recommended levels, and will be analysed logistic regression adjusting for all known prognostic factors, data will be presented as odds ratios and their corresponding confidence intervals. Secondary analyses will be undertaken using the appropriate method for the outcomes, controlling where appropriate for intake values and other known prognostic variables using analysis of covariance. Simulations will be undertaken to encompass both screening approach groups and intention to treat analysis will be undertaken on both groups.

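### The clustering inflation of 2.7 does not follow from the stated ICC and cluster size (they give 6.2), so a pairwise comparison of 5% with 18% has about 50% power, not 80%

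*Protocol*

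**What the plan says.** In the Protocol, under Sample size calculation, the primary outcome is the proportion drinking within recommended levels at 6 months. The assumed effect is "5% reduction in the control group and 18% in the brief intervention group", tested "at the 5% significance level with 80% power, for a 2-sided test". This "requires 109 patients in each of the 3 groups, a total of 327". Attrition is then added, since "the potential loss to follow-up across groups is of the order 25" per cent, giving 131 in each group.

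For clustering, the literature and earlier primary care trials "suggest an intra-class correlation coefficient of 0.04 is appropriate". The text continues: "Assuming a cluster size of the order 131 patients this inflates the sample size calculation by a factor of 2.7". The result is 393 per group and 1179 in all, with at least 882 followed up.

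The Synopsis and Table 1 both give 131 as the number per AED. The Design section and Table 1 give three AEDs per intervention and three per screening method.

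Two statements extend the power claim to screening. The sample size section says: "Powering the study in this way will also account statistically for appropriate outcomes for screening approach and screening method". The Synopsis says that "each of the three elements (screening tool and intervention) can be analysed independently with sufficient power".

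**The concern.** The ICC and the cluster size are both printed, and the factor drawn from them is less than half what they imply. This is a wrong result from stated inputs, not a detail left for an analysis plan.

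The factor carries the whole step from an individually randomised sample to a cluster trial with three AEDs per arm. If it is wrong, the trial has roughly even odds of missing the effect it was sized for while being described as having 80% power. A non-significant difference from the leaflet could then be given more weight than it deserves. The screening comparisons also have three AEDs per arm and take their claim of adequate power from the same calculation.

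**Working it through.** **Inputs** (Protocol, Sample size calculation, Design and Table 1): p1 = 0.05, p2 = 0.18, d = 0.13; two-sided 5%, 80% power; 25% loss; ICC 0.04; 131 recruited per AED; 3 AEDs per arm; 882 followed up, which is 294 per arm and 98 per AED.

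**1. Reproduce 109.**
- Pooled two-proportion formula: n = [1.96 x sqrt(2 x 0.115 x 0.885) + 0.8416 x sqrt(0.0475 + 0.1476)]^2 / 0.13^2 = 93.3.
- With continuity correction: (93.3/4) x [1 + sqrt(1 + 4/(93.3 x 0.13))]^2 = 108.2, so 109.
- The figure reproduces, and it identifies the formula behind the plan.

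**2. Attrition step.** 109/0.75 = 145.3, so 146, not 131. (131 matches 109 x 1.2 = 130.8.) The 393 given here as patients per intervention is 3 x 131, the total over three groups.

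**3. Design effect, 1 + (m - 1) x ICC.**
- m = 131: 1 + 130 x 0.04 = 6.20.
- m = 98: 1 + 97 x 0.04 = 4.88.
- To obtain 2.7: m = 1 + 1.7/0.04 = 43.5, or ICC = 1.7/130 = 0.013 at m = 131, or 1.7/97 = 0.0175 at m = 98.
- 131/3 = 43.7, so dividing 131 over three AEDs may be the source. That is an inference; the protocol does not say so.

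**4. How 393 arises.** 109 x 2.7 / 0.75 = 392.4, so 393. On the analysed sample, 294/2.7 = 108.9, which is the 109 required. The 393 and the 80% therefore both depend on 2.7.

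**5. Effective sample per arm at ICC 0.04.** 294/4.88 = 60.2. Using everyone recruited, 393/6.2 = 63.4. The requirement is 109.

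**6. Power for 5% vs 18%, two arms of three AEDs, effective n = 60.2.** The standard errors are s0 = sqrt(0.20355/60.2) = 0.0581 (pooled) and s1 = sqrt(0.1951/60.2) = 0.0569 (unpooled).

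| Method | Calculation | Power |
|---|---|---|
| Continuity-corrected (the formula that gives 109) | Phi[(0.13 - 1/60.2 - 1.96 x s0)/s1] | 50% |
| Normal, uncorrected | Phi[(0.13 - 1.96 x s0)/s1] | 61% |
| AED-level t, 6 df | noncentral t, ncp = 0.13/s1 = 2.28 | 48% |
| AED-level t, 4 df | same ncp | 42% |

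Entering 63.4 instead of 60.2 raises each figure by about 2 points.

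**7. Ceiling.** As m grows, 3m/[1 + (m - 1) x 0.04] tends to 3/0.04 = 75 per arm. At 75, power is 61% (corrected), 71% (uncorrected) and 49-57% (t on 4-6 df).

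**8. Effect detectable with 80% power at effective n = 60.2.** Solving the step 6 formulas for p2 with p1 = 0.05 gives about 22% (uncorrected), 25% (corrected) and 26-29% (t on 6-4 df).

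**9. ICC at which 80% would hold with 98 per AED.** Solving the same formulas gives about 0.0175 (corrected), 0.022 (uncorrected) and 0.008-0.013 (t on 4-6 df).

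**The case against.** **The 393 is internally consistent.** A reader might compute 131 x 2.7 = 354 and conclude that 393 does not follow even from 2.7. The document's figures do not support that: 109 x 2.7 / 0.75 gives 392.4, and 393 x 0.75 = 294.75 fits the 882 expected at follow-up. The derivation from 2.7 stands; 2.7 itself does not. For the same reason, the slip from 146 to 131 leaves 393 unaffected.

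**Nine AEDs could still reach 80% for some contrast.** A reader might infer that no comparison in this design can. That goes too far, because the ceiling of 75 belongs to pairwise contrasts of three AEDs with three. The second item under Hypotheses sets counselling and brief advice against the leaflet and could be read as six AEDs against three. For that contrast the pooled-variance normal approximation gives 70% at the planned size and 81% with unlimited patients. The unpooled version is more favourable: the standard error is sqrt(0.0475/60.2 + 0.1476/120.5) = 0.0449, and Phi(0.13/0.0449 - 1.96) is about 83% at the planned size. With a t reference on 6-7 df, even unlimited patients leave it at about 61-79%. The sample size section, however, sizes each of three groups separately and does not base its 80% on a combined contrast.

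**The low power figures assume a test the protocol does not plan.** This is fair. Planned analysis specifies logistic regression adjusted for prognostic factors, with multi-level modelling to explore interactions. The 42-48% is a sensitivity figure for an AED-level t test. The like-for-like figure is 50%.

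**The true ICC may be below 0.04.** It may, but the protocol adopts 0.04 and gives no lower value.

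**Conclusion.** The point holds. The stated ICC and cluster size give a design effect of 6.2 (4.88 on followed-up patients), not 2.7, and no standard variant of the formula recovers 2.7. The effective sample is about 60 per arm, or 55% of the 109 required (60.2/109). Pairwise power is about 50% on the protocol's own formula and below 80% by every method tried; the spread of 42-61% reflects the choice of method. Further recruitment at the same AEDs cannot restore 80% for a pairwise contrast.

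This rests on ICC 0.04, equal cluster sizes, 25% loss, and the 5% and 18% proportions. It does not show that every contrast falls short, nor that 0.04 is the right ICC for AEDs. The attrition step (131 for 146) and the label on the first 393 are separate slips that do not change this conclusion. The claims of sufficient power for screening have no support, because the only calculation offered contains this error and was made for the intervention outcome.

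**What to change.** Keep nine AEDs and 1179 patients, and rewrite the sample size paragraph:

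- Give the design effect as 6.2 (4.88 on followed-up patients) and the effective sample as about 60 per arm.
- State the resulting power for 5% vs 18% and the effect detectable with 80% power, each labelled by method.
- Correct 109 with 25% loss to 146, and describe 393 at that step as the total over three groups.

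Alternatively, state and justify a lower ICC specific to AEDs, since 0.04 is drawn from the literature and primary care trials. Say that 80% needs about 0.0175 with continuity correction, about 0.022 without, and less again if few-cluster degrees of freedom are used.

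Adding AEDs would also work arithmetically: 109 x 4.88 / 0.75 = 709 recruited per arm, and 709/131 = 5.4, so six AEDs per arm or 18 in all. The Design section already says that 18 exceeds the number likely to take part.

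Remove the statements in the Synopsis and the sample size section that the same calculation gives enough power for screening. Describe those comparisons as estimation, with confidence intervals that account for clustering by AED.

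The cost is wording and a less favourable stated power. No extra patients or sites are needed.

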Due to the nested factorial nature of the study, we will use multi-level modelling to explore potential interactions between each of the levels nested within the trial.

Practice and patient factors will be utilised as part of regression model to explore possible prognostic factors that impact on outcome. Interaction analysis will explore any possible interactions between practice and patient characteristics and outcome. The efficacy of the interventions will be explored with a secondary analysis utilising a per protocol approach. A sub-group of the trial population, those who engaged in the allocated treatment will be utilised for this analysis.

Ethical and Research Governance Approval

We will seek Multi-centre ethical approval for the trial plus local agreement from all relevant LRECS. In addition, research governance approval will be sought from all relevant acute NHS trusts.

Project Timescales and Funding

The trial duration will be 2 years beginning at the point that ethics and governance approval has been secured.

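### The primary-analysis sentence names no adjustment for AED clustering although AEDs are the unit of randomisation; followed as written, type I error per contrast is about 15–38% (ICC 0.01 to 0.04), not 5%

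*Protocol*

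**What the plan says.** The Design section and Table 1 of the protocol allocate nine AEDs, three to each intervention and three to each screening method, with one AED in each of the nine cells.

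The Sample size calculation section defines the endpoint: "The primary outcome for this study is the proportion of patients who consume alcohol within recommended levels at 6 month follow up". It then states: "The proposed study involves a cluster design and requires a statistical adjustment to account for any potential cluster effect". On the size of the clustering, the literature and the team's earlier trials "suggest an intra-class correlation coefficient of 0.04 is appropriate".

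The Planned analysis section gives the model for that endpoint: it "will be analysed logistic regression adjusting for all known prognostic factors, data will be presented as odds ratios and their corresponding confidence intervals". Nothing in this sentence or around it mentions AEDs as clusters.

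Multi-level modelling comes in a later paragraph of the same section, with a limited purpose: "we will use multi-level modelling to explore potential interactions between each of the levels nested within the trial". Practice and patient factors also enter a regression there, but to search for prognostic factors and interactions, not to estimate the intervention effect.

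**The concern.** The protocol allows for clustering when it sets the sample size and leaves it out when it names the primary test. Each intervention is delivered in only three AEDs, so part of any difference between arms is simply a difference between hospitals. A logistic regression that treats patients as independent has no term for that part. Its standard errors are too small, its confidence intervals too narrow, and a chance difference between one set of three hospitals and another can be reported as an intervention effect. This is the test of the trial's main hypotheses. Because the protocol fixes both the model and its output (odds ratios with confidence intervals), an SAP that followed the sentence literally would inherit the fault.

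**Working it through.** **Inputs, all from the Sample size calculation and Design sections.** Rates of 5% and 18%; two-sided 5% level; 80% power; ICC 0.04; inflation factor 2.7; 131 patients recruited per AED; at least 882 followed up at 6 months, so 882/9 = 98 per AED and 3 × 98 = 294 per arm; three AEDs per arm.

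**The plan's own figure.** For two proportions, n = [1.96 √(2 p̄ q̄) + 0.8416 √(p1 q1 + p2 q2)]² / d², with p̄ = 0.115 and d = 0.13. This gives (0.884 + 0.372)² / 0.0169 = 93.3, so 94 per group. With the continuity correction, (93.3/4) × [1 + √(1 + 4/(93.3 × 0.13))]² = 108.2, so 109 per group. The stated 109 is reproduced.

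**Type I error when clusters are not modelled.**
- Design effect DE = 1 + (m − 1) × ICC = 1 + 97 × 0.04 = 4.88.
- Standard errors are too small by √4.88 = 2.2.
- Effective patients per arm: 294/4.88 = about 60.
- Actual two-sided level = 2 × [1 − Φ(1.96/√DE)] = 2 × [1 − Φ(0.887)] = 37.5%.

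The analytic figures were checked by simulation: 200,000 beta-binomial replicates per setting, 3 versus 3 AEDs, no true effect, true proportions from 5% to 18%, unadjusted patient-level tests.

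| Setting | DE | Analytic level | Simulated level |
|---|---|---|---|
| ICC 0.04, 98 per AED | 4.88 | 37.5% | 35–38% |
| Protocol's factor, taken as given | 2.70 | 23% | not run |
| ICC 0.02, 98 per AED | 2.94 | 25% | 23–25% |
| ICC 0.01, 98 per AED | 1.97 | 16% | 15–16% |
| ICC 0.005, 98 per AED | 1.485 | 11% | 9.5–10.7% |
| ICC 0.04, 131 per AED (no loss) | 6.20 | 43% | 42–43% |

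The factor of 2.7 does not itself follow from 131 per AED at ICC 0.04, which gives 1 + 130 × 0.04 = 6.2. That is a separate point; 2.7 appears here only to show that the conclusion survives the protocol's own allowance.

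**What a valid analysis does.** At ICC 0.04 and 98 per AED, with no true effect, a t test on AED proportions rejects in about 4–5% of replicates. This holds for 3 versus 3 AEDs (4 df), for all nine AEDs without screening method (6 df), and for all nine with it (9 − 1 − 2 − 2 = 4 df).

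**What it costs in power.** With true proportions of 5%, 18% and 18%, power for 5% versus 18% is about 43% on 6 df and 37% on 4 df. The normal approximation with 60 effective patients per arm gives 61%, and it ignores the small number of AEDs.

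**Why the AED summary should not be a log-odds.** At a 5% rate, ICC 0.04 and 98 patients, the beta-binomial chance of no events in an AED is 13.6%. The chance that at least one of three control AEDs has none is 1 − (1 − 0.136)³ = about 35%. The log-odds is then undefined.

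**The case against.** The strongest reply is that silence is not a decision. A logistic regression can carry a random intercept or cluster-robust errors, the investigators plainly know that the data are nested, and the estimator and degrees-of-freedom correction are usually left to an SAP, which is not to hand.

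Part of this stands, and it limits what may be said. A reader might infer that the protocol chose to ignore clustering; it does not say so. A reader might also infer that the screening factor is left out of the primary model, or that only patient-level covariates are meant. The sentence lists no covariates, so neither can be asserted. The absence of a few-cluster reference distribution is likewise a detail that an SAP may supply.

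Nor is 37% a flat property of the plan. It applies to one pairwise contrast, at 98 per AED, with covariates that explain none of the between-AED variance. The ICC of 0.04 draws on the literature and on experience in primary care and is not stated to be specific to AEDs.

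What does not stand is that the point is mere missing detail. The protocol names the primary model, names a different and exploratory use for multi-level modelling, and says elsewhere that clustering needs adjustment. Covariates are an unlikely rescue: reducing the ICC from 0.04 to 0.005, which removes seven-eighths of it, still leaves about twice the nominal error. AED fixed effects cannot help, because each AED delivers only one intervention.

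**Conclusion.** The primary-analysis sentence is wrong as written: it names no cluster adjustment for a comparison between arms of three randomised AEDs, and so conflicts with the protocol's own sample size section. Followed literally, the type I error for one pairwise intervention contrast is about 35–38% at the protocol's ICC with 98 followed up per AED, 23% at its own factor of 2.7, and about 15–16% at ICC 0.01. The exact figure depends on the ICC, the cluster size and how much between-AED variation the covariates absorb; at every value examined it is about twice the nominal 5% or more. The supported claim is that the protocol fails to name the adjustment in the one sentence where it is needed.

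**What to change.** Replace the sentence with a primary analysis that respects AEDs and includes both intervention and screening method. There are two workable forms:

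- A two-stage analysis: adjust at patient level for prespecified baseline covariates, form an adjusted proportion or an observed-minus-expected residual for each AED, then regress these nine values on intervention and screening method and test on t with 4 df. Do not use AED log-odds.
- A mixed logistic model with an AED random intercept, both randomised factors and a small-sample degrees-of-freedom correction.

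The 4–5% error rates above come from unadjusted AED proportions. Neither the covariate-adjusted version nor the mixed model was simulated, so the one chosen should be checked at the planned size. The Synopsis stratifies the screening randomisation by median admission rate. The plan should say whether this enters the model; as a two-level term it would leave 3 df.

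Apply the same rule to the secondary patient outcomes, including the analyses of covariance.

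Sites, recruitment and data collection do not change. The cost is wider, correct confidence intervals and a power statement that must be rewritten: at ICC 0.04, about 37% on 4 df (43% on 6 df) for 5% versus 18%, in place of 80%. That loss should be disclosed; it is no reason to keep an analysis that does not hold its level.

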However, it is unclear which approach is most effective in identifying cases in the typical AED setting. The modified PAT (SIPS-PAT) is a targeted screening tool which is applied in cases with presenting conditions commonly associated with alcohol misuse. The original PAT has been used at St Mary’s Hospital embedded in the standard clinical assessment process. SASQ on the other hand has been studied in PHC and, based on our pilot research, is more likely to be adopted by busy AED staff. The FAST has been used mainly in a research screening context to establish prevalence rather than as a clinical tool. Also this single question in the modified SASQ will identify individuals whose level of drinking is more likely to lead to AED attendance, and is the same first item of the FAST questionnaire, which was found to identify 50% of hazardous and harmful drinkers (Hodgson et al., 2002).

Brief intervention implementation conditions

1. *Control condition:* AED staff (including dedicated AHWs) in the control condition will be trained to apply the appropriate screening method and record the screening outcome, will feedback the result of screening to patients and offer them a patient information leaflet (PIL. The PIL from the Drink-Less Programme and has been extensively pre-tested with clinicians and patients in PHC and will be used in this trial. The PIL will also contain a number for Drinkline where the patient can access further information). The PIL to be used in this trial will be ‘Alcohol and Sensible Drinking’ as in the PHC study.

2. *Brief Advice condition:* AED staff (including dedicated AHWs)will be trained to carry out screening and deliver up to 5 minutes of simple structured brief advice for hazardous and harmful drinkers presenting to the AED, using the Drink-Less brief intervention materials (level 1) as in the PHC study. Patients in this condition will also receive a Patient Information Leaflet (PIL) as above, including a number for Drinkline.

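### The primary model names neither the second randomised factor (screening method) nor the AED, so differences between screening tools may enter the error of the intervention comparison

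*Protocol*

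**What the plan says.** The Synopsis and Design sections of the Protocol describe a 3x3 factorial cluster trial. Nine AEDs are randomised to three interventions and three screening methods, and Table 1 shows one AED in each cell. The Synopsis says each element "can be analysed independently with sufficient power to make meaningful interpretation of relative effectiveness".

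Under Inclusion criteria, a positive result on the allocated tool is what makes a patient eligible. The tools differ in whom they reach. SIPS-PAT is applied only to presentations linked with alcohol misuse, while FAST and the modified SASQ are universal. The single modified SASQ question "is the same first item of the FAST questionnaire, which was found to identify 50% of hazardous and harmful drinkers".

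The primary outcome is "the proportion of patients who consume alcohol within recommended levels at 6 month follow up". Planned analysis says it "will be analysed logistic regression adjusting for all known prognostic factors", by intention to treat. It lists no covariates and names neither screening method nor AED. The next paragraphs bring in multi-level modelling to explore interactions, and practice and patient factors to explore prognosis. Neither is tied to the primary comparison.

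**The concern.** The trial randomises AEDs on two crossed factors, and the second acts as a block for the first. If the tools enrol drinkers of different prognosis, AEDs in the same intervention arm will differ systematically because they use different tools. An analysis with AED-level error but no screening term counts that difference as random variation between AEDs. The interval for the intervention effect is then too wide and the test rejects too rarely. With only nine AEDs there is little precision to spare.

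The omission of AED matters more. Without an AED term, patients within a department are treated as independent, although the Sample size calculation section assumes an ICC of 0.04.

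**Working it through.** **Inputs from Sample size calculation.** Success rates are "5% reduction in the control group and 18% in the brief intervention group", tested "at the 5% significance level with 80% power, for a 2-sided test". ICC is 0.04 and loss to follow-up is 25%. The expected 882 patients followed over 9 AEDs give 98 per AED.

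**The plan's own figure.** It "requires 109 patients in each of the 3 groups, a total of 327". The two-proportion formula for 5% v 18% gives 94 per group without continuity correction and 109 with it, so 109 reproduces.

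**Assumption.** The Protocol gives no between-tool difference in outcome. I place the three tools at -s, 0 and +s around the mean and vary s.

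**Plain logistic regression, as written.** With tool effects of 0.5 logit either side, the standard error of the log odds ratio is 0.299 with the tool omitted and 0.301 with it included. The odds ratio is 4.08 against 4.17. The tool hardly matters in this model. Ignoring AED does: a patient-level test has simulated type I error of about 37%.

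**AED-level error, analytic.** At the mean rate (5 + 18)/2 = 11.5%:

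- Variance of an AED proportion: v = 0.115 x 0.885 x (0.04 + 0.96/98) = 0.00507, SD 0.0712.
- SE of an intervention contrast: sqrt(2v/3) = 5.8 points.
- Tool included, 9 - 1 - 2 - 2 = 4 df: half-width of the 95% interval 2.776 x 5.8 = 16.1 points, whatever s is.
- Tool omitted, 6 df: the residual variance has expectation v + s², because the tools add 3 x 2s² to the sum of squares and 6s²/6 = s². The half-width is 2.447 x sqrt(2(v + s²)/3): 14.2 points at s = 0, 14.8 at s = 2 points and 16.3 at s = 4 points.
- Break-even: s² = v x ((2.776/2.447)² - 1), so s is about 3.8 points. A simulation of AED proportions puts the break-even for power nearer 3 points.

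**AED-level error, simulated.** Beta-binomial data with rates 5%, 18% and 18%, ICC 0.04, 98 per AED, and tool effects on the logit scale so that all rates stay possible. At 0.5 logit the leaflet AEDs are at 3.1%, 5% and 8.0%, and the brief advice AEDs at 11.7%, 18% and 26.6%. Null rejection is simulated with all arms at 11.5%.

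| Tool effect (logit, either side) | Null rejection, omitted v included | Power, omitted v included |
| --- | --- | --- |
| 0 | about 5% v 5% | 43% v 37% |
| 0.25 | about 4% v 5% | 37% v 35-36% |
| 0.5 | about 2% v 4% | 24% v 32% |
| 0.75 | 0.7% v about 4% | 11% v 26% |

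The curves cross at about 0.3 logit. Power with the tool included also falls down the table, in part because effects that are constant on the logit scale are not additive on the proportion scale, and with one AED per cell that departure goes into the residual. Both columns lie far below 80% because error is taken between nine AEDs. That is a separate matter; only the difference between the columns bears on this point.

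**The case against.** Four objections carry weight.

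- **The text does not exclude screening method.** The prognostic factors are undefined and could cover it, and a covariate list may sit in a statistical analysis plan that is not shown. This stands as a limit: the fault is that the factor is not named. A reader might go further and take the Synopsis wording on independent analysis as a decision to compare interventions marginally. The document does not support that, since the phrase fits the ordinary factorial property that each factor can be assessed separately. But this is more than a missing covariate list: the Protocol itself fixes the model and adjustment rule, and leaves out a factor that the trial randomises.
- **The too-wide interval is not a property of the model as written.** This is correct. With no AED term the tool barely changes the standard error, and ignored clustering errs the other way. The conservative test arises only once error is taken between AEDs.
- **The size is assumed.** This is also correct. A reader might try large additive shifts, but 5 points either side takes a 5% control AED to 0%, and 8 points takes it to -3%. The logit-scale results avoid this. Adjustment for baseline AUDIT would also absorb some of the case-mix difference, which the simulation does not model.
- **Balance prevents confounding.** A reader might infer that the point estimate is biased by tool mix. Table 1 plans 131 per AED and one AED per cell, so intervention and tool are orthogonal. The Synopsis does say "Each AED will recruit a minimum of 131 patients who are hazardous or harmful drinkers into the trial", so sizes may differ. Suppose one arm recruits 131, 131 and 200 across tools at -4, 0 and +4 points, and the comparator 131 in each AED. A patient-weighted contrast then shifts by (200 - 131) x 4/462 = 0.6 points. That is minor, and it is zero if AEDs are weighted equally.

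**Conclusion.** The point holds in a limited form. The primary model names neither screening method nor AED, and the exploratory multi-level models do not repair this for the primary comparison. Of the two omissions, the missing AED term is the more serious.

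With AED-level error in place, omitting screening method costs about 8 points of power (24% v 32%) and lowers null rejection to about 2% if the tools differ by 0.5 logit either side. If they do not differ, including it costs about 6 to 7 points. These figures assume ICC 0.04, 98 followed per AED, equal AED sizes and no other covariates. The between-tool difference is my assumption. What favours inclusion is that the tools select different patients by design, and that the AED-level test then stays near its nominal level, slightly below it, across the range shown.

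**What to change.** In Planned analysis, state that the primary model contains intervention (3 levels) and randomised screening method (3 levels) as main effects, both kept whatever their significance. State also that error is taken at AED level by a method suited to nine clusters, for example a two-way analysis of AED-level results on 4 degrees of freedom, or a mixed logistic model with a small-sample correction.

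This needs wording only, with no change to conduct or data. The statistical cost is the fall from 6 to 4 residual degrees of freedom, a net loss if the tools differ by less than about 3 to 4 points, or 0.3 logit, either side. The choice should be fixed before outcome data are seen, because it could otherwise be made on the result.
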